### Participants

The target population will be children aged 6 to 12 years. To be eligible for the study, children must be enrolled in primary school and attending one of the 10 project institutions or partner schools and residing in socially deprived neighborhoods in Porto identified as being at risk of social exclusion. Children with a cognitive deficit, a neurological disorder, or a global developmental disorder will not be eligible.

On the basis of an expected medium effect size (Cohen *d*=0.5), an α error probability of .05, and 90% statistical power, using the difference of means between 2 independent samples with a 2:1 allocation ratio, we estimate that a total of 156 participants will be required to detect significant results (n=104, 66.7% in the experimental group and n=52, 33.3% in the control group). We anticipate fewer participants in the control group at the end of the study due to its higher likelihood of dropout [32]. Participants in the control group are not directly involved in the intervention, which may decrease their perceived benefit, reduce their engagement, and increase the possibility of withdrawal compared with those actively participating in the experimental intervention. However, if this occurs, the results will not necessarily be biased [33]. This consideration justifies the use of a 2:1 allocation ratio, ensuring sufficient statistical power despite the potential for unequal group retention rates. To account for an estimated 30% dropout or refusal rate, we will initially recruit approximately 223 participants.

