## Results

The project was funded in September 2023. Participant recruitment started in March 2024 and concluded in July 2025. As of April 2024, a total of 179 participants had been enrolled. Data collection was completed in July 2025, and analysis is expected to begin in April 2026. The final results are anticipated to be published in September 2026. A CONSORT (Consolidated Standards of Reporting Trials) flow diagram is presented in Figure 2.

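### Higher expected control dropout is given as the reason for a 2:1 allocation that makes the control arm the smaller one; the reasoning is reversed, and the stated assurance of power under unequal retention is not supported.

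*Protocol article*

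**What the plan says.** All of this is in the Participants section of the protocol article.

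- The size is set by "On the basis of an expected medium effect size (Cohen *d*=0.5), an α error probability of .05, and 90% statistical power". The calculation is a two-sample comparison with twice as many intervention children as controls. The result is 156 children, 104 intervention and 52 control. Sidedness is not stated.
- Retention is expected to differ by arm: "We anticipate fewer participants in the control group at the end of the study due to its higher likelihood of dropout".
- From that expectation the article concludes: "This consideration justifies the use of a 2:1 allocation ratio, ensuring sufficient statistical power despite the potential for unequal group retention rates".
- The inflation follows: "To account for an estimated 30% dropout or refusal rate, we will initially recruit approximately 223 participants". No dropout rate by arm and no recruitment target by arm is given.

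The Methods part of the Abstract gives 104 and 52 as the numbers of children to be recruited.

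**The concern.** For a difference between two independent means, precision is limited by the smaller arm. If controls are expected to be lost at a higher rate, that argues for recruiting relatively more of them. The article draws the opposite conclusion and presents it as a safeguard.

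The inflation step does not supply the safeguard either. It applies a single rate to the total, although unequal loss is expected two sentences before the 2:1 ratio is defended.

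At stake is a stated property of the design. A reader of a null result would believe that the trial had been protected against unequal retention, when its allocation makes it more exposed to it.

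**Working it through.** **Inputs.** From Participants: d = 0.5 (SD = 1), α = .05, power 90%, ratio 2:1, 104 and 52 required, 30% loss, 223 recruited. Assumed here: the dropout rates by arm, and a 2:1 split of the 223 into about 149:74. All power figures use the noncentral t distribution and ignore clustering.

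**1. Reproducing 156.** With r = 2, the control arm needs (1 + 1/r)(z_α + z_β)²/d².
- One-sided: 1.5 × 2.926² / 0.25 = 51.4, so 52 controls and 104 intervention, total 156. This matches.
- Two-sided: 1.5 × 3.242² / 0.25 = 63.0, rounded up to 64 controls and 128 intervention, total 192. This does not match.

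The stated figure is therefore a one-sided one.

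**2. Reproducing 223.** 156/0.70 = 222.9, so 223. This matches, with one rate for everyone. From 149:74, a 30% loss in each arm leaves 104.3 and 51.8, that is 104:52.

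**3. Power by final arm sizes.** The noncentrality is δ = d × √(n₁n₂/(n₁ + n₂)), with n₁ + n₂ − 2 degrees of freedom. Overall loss is held at 30% from 149:74.

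| Loss, intervention/control | Final sizes | δ | Power, one-sided | Power, two-sided |
|---|---|---|---|---|
| 30%/30% | 104:52 | 2.944 | 90.1% | 83.3% |
| 25%/40% | 112:44 | 2.810 | 87.6% | 79.7% |
| 20%/50% | 119:37 | 2.656 | 84.1% | 75.2% |

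The total stays at 156 in every row; only the split changes. The cost against the first row is 2.5 and 6.0 points one-sided, and 3.6 and 8.1 points two-sided.

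**4. The same 223 recruited 1:1 (111.5 per arm), same loss rates by arm.**

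| Loss, intervention/control | Final sizes | Power, one-sided | Power, two-sided |
|---|---|---|---|
| 25%/40% | 83.6:66.9 | 91.8% | 85.7% |
| 20%/50% | 89.2:55.8 | 89.8% | 82.9% |

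Equal recruitment loses more children in total here (32.5% and 35% instead of 30%), because more of those recruited are controls. It still has more power.

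**5. Why this is general.** With retention R_I and R_C and equal SDs, the variance of the difference is proportional to 1/(N_I·R_I) + 1/(N_C·R_C). For a fixed total recruited it is smallest at N_I/N_C = √(R_C/R_I). If controls are retained less well, this ratio is below 1: √(0.60/0.75) = 0.89 and √(0.50/0.80) = 0.79. Higher control dropout moves the best ratio towards more controls, away from 2:1.

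**The case against.** The strongest defence is that 2:1 describes the composition expected at the end of the study, since the sentence on dropout speaks of that time point. A total of 223 could then be split differently at recruitment. For example, 139:84 with losses of 25% and 38% ends at 104.3:52.1, and a single overall 30% would be consistent with unequal dropout. This shows that the conflict between 223 and unequal loss rests on the 149:74 split, which the article does not print. But the article calls 2:1 an allocation ratio, its Abstract gives 104 and 52 as children to be recruited, and no other split is stated. If 223 were recruited 1:1, ending at 104:52 would need about 53% control loss and 7% intervention loss, which appears nowhere. The defence leaves the passage ambiguous; it does not make the stated reason right.

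A second objection is size, and it stands. The rates by arm are assumptions, the one-sided loss is modest, and one-sided power stays above 80% in both scenarios. The fall from 90% to 83% at 104:52 comes from sidedness and must not be charged to unequal retention.

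Three stronger readings are tempting but not supported:
- A reader might combine the 30% with the statement "As of April 2024, a total of 179 participants had been enrolled" and conclude that the trial fell short. That count is dated about one month after recruitment opened in March 2024, and recruitment ran to July 2025. The flow diagram, which may give final numbers, was not available for this check. The 30% also covers refusal, which enrolled children may already have passed.
- A reader might infer attrition bias. The article predicts a higher control dropout rate, not loss related to outcome.
- A reader might ask for a delta-adjusted analysis because dropout depends on arm. Missingness that depends on arm alone is missing at random given arm, and group is in the planned model.

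Finally, 2:1 may have a sound practical reason, such as which neighbourhoods were due to start in year 2. That would justify the ratio, but it is not the reason given.

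**Conclusion.** The point holds as an unsupported claim about power with its reasoning reversed. Against the protocol's own 90% target, unequal loss with the overall rate at 30% costs about 2.5 to 6 points one-sided, or about 4 to 8 two-sided, in the two scenarios. The 52 controls leave no margin to absorb it. The direction does not depend on the scenarios: whenever controls are retained less well, a 2:1 ratio in favour of the intervention has less power than 1:1 for the same number recruited. The size does depend on them, and on recruitment at 149:74, d = 0.5 and no clustering. The claim falls short of the 90% target; it does not follow that the trial is uninformative.

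**What to change.** In the Participants section:

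1. Delete the statement that 2:1 ensures power under unequal retention.
2. Give the actual reason for the 2:1 ratio, or give none.
3. State the dropout assumed in each arm, and restate power from those rates and the final enrolled numbers by arm, naming the sidedness of the test.

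Data collection is complete, so the allocation cannot change. The cost is a few sentences and a small power table, and a stated power that will look less favourable. The restatement changes no design decision, but it tells readers how much a null result can bear.

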### Procedures

The researchers will coordinate with established partner schools and social projects in 10 neighborhoods to disseminate information about the study’s objectives and procedures. Local partners will inform caregivers about the study’s purpose and procedures, invite them to participate, and obtain informed consent from legal guardians for those willing to participate.

Furthermore, verbal assent will be sought from the children themselves to ensure their willingness to participate. Data collection will preferably be conducted in person. Online data collection will only be carried out if the participant cannot complete the form in person or because of a justified absence and requests online completion. In cases where online completion is requested, the participant’s or guardian’s email will be collected, and a link will be sent to access the Qualtrics platform. Identifiable data, such as email addresses, will never be stored together with the raw data. To minimize any differences between the modalities, the collection method will be recorded for later analysis. Statistical control of any effects of the modality on the results will also be considered. Only those children whose parents or legal guardians have provided informed consent and who have also given their own verbal assent will be included in the study. Due to the noninvasive and low-risk nature of the intervention, a formal data monitoring committee is not required. Any minor issues arising during the sessions will be addressed immediately through internal safety procedures. To ensure data confidentiality, the following procedures will be implemented: (1) using a system code for each research protocol, (2) separating the research protocol and informed consent to maintain participants’ anonymity, (3) collecting only personal data necessary for research purposes, and (4) entering data in statistical software and analyzing them solely in a collective manner. We will apply Portuguese law and European Union directives regarding personal data protection. Data will be anonymized and stored on encrypted university-based electronic servers, with restricted access to the research team. Participants’ personal information will not be shared with third parties. Deidentified datasets will be made accessible in a repository for verification and reuse. All procedures, objectives, and expected contributions will be communicated in advance to the participants and their guardians. However, interested parties will be able to obtain more detailed information about the study by contacting the principal researcher by email. Additionally, after the study’s conclusion, an information meeting will be held at the partner institutions, to which guardians will be invited. The results and conclusions of the study will be made available to participants and their guardians through the institutions or schools involved, where they will be able to access a QR code linking to a webpage containing the reports, articles, and communications of the study. Flyers with a summary of the main results will be delivered to the partner institutions for distribution to the children and legal guardians.

This trial includes 2 assessment waves: (T1) baseline and (T2) postintervention assessment, 9 months after baseline. A participant timeline is provided in Figure 1. At baseline (T1), caregivers and children will provide sociodemographic information, details on family mental health history and relevant adverse RLE, and information on resources used by participants. Given that some children may experience difficulties with reading and interpreting questions, all children will rate their self-concept and HRQoL, ensuring uniformity in data collection across participants. Additionally, teachers or social project technicians (depending on the cluster) will report on the children’s behaviors, emotions, and relationships. Following the baseline assessments, participants will be assigned to either the control or intervention group without randomization. The nonrandomized assignment arises because the clusters, defined by schools or social projects, are fixed and cannot be restructured for randomization purposes. At postintervention assessment (T2), the same protocol as at baseline (T1) will be followed: caregivers will provide details on the family mental health history, relevant adverse RLE, and resources used by participants. Children will also rate their self-concept and HRQoL, while teachers or social project technicians will report on the children’s behaviors, emotions, and relationships.

**Figure 1 figure1:**
[figure not shown]
Participant timeline—schedule of enrollment, interventions, and assessments. CHU9D: Child Health Utility 9D; PEARLS: Pediatric Adverse Childhood Experiences and Related Life Events Screener; PSPCSA-YC: Pictorial Scale of Perceived Competence and Social Acceptance for Young Children; RUQ: resource use questionnaire; SDQ: Strengths and Difficulties Questionnaire; SPPC: Self-Perception Profile for Children.

### The Art Intervention Community Galleries

The art intervention will consist of 2 parts. First, implementation of a 1-hour visual arts session (eg, painting, drawing, and printing techniques exercises) once a week for 9 months with the experimental group. Sessions are delivered in person, in real time, in a group format of 10 to 20 children per venue, across 10 community venues situated in socially deprived neighborhoods of Porto. The activities will be guided by a theme (emotions) by a qualified art facilitator (artist) with prior experience working with children to obtain a final individual artistic product. The session structure is adaptive: while the thematic focus and the artistic medium remain consistent, the facilitator adjusts pacing, complexity, and sequencing in response to participants’ receptivity and motor and cognitive capacities, given that children range in age. Each session typically includes (1) an introductory phase in which the facilitator introduces the theme and demonstrates a technique using materials such as paints, watercolors, pencils, canvas, paper, and accessible printmaking plates; (2) an active creation phase in which participants produce individual artwork independently within the group setting; and (3) an informal sharing phase in which children exchange ideas, difficulties, and improvements with peers. Through strategies such as repetition, observation, and imagination, the exercise promotes a spirit of inquiry and learning. Peer contact, shared learning, and a feeling of community are all made possible by the group-based approach. The facilitator will provide support, motivation, and technical training while guiding participants through the creative process and will also monitor adherence by collecting signatures to confirm attendance at the sessions. Using narrative-building and dialogue-based methods, the artist will encourage children to share their stories, experiences, and perspectives through art. Narrative-based techniques use narrative to investigate human experiences, emotions, and perspectives. By constructing tales via art, individuals may make sense of their experiences, manage complicated emotions, and get a better understanding of themselves. Dialogue-based strategies enable people to have meaningful conversations about their experiences. The intervention is guided by several interrelated principles. Self-expression is a foundational orientation, with participants afforded autonomy to represent their emotions and experiences according to their own visual preferences within a technically guided framework. Individual self-worth is promoted through the public display of artwork in community exhibitions. Emotional exploration constitutes the thematic spine of the program, providing a coherent and recurring psychological framework across all sessions. The session design also promotes present-moment engagement through attentive sensory involvement with materials, including awareness of hand movements, textures, and visual composition, as well as aesthetic appreciation of color, form, and harmony. Creativity and personal narrative are central to the activity design, and the group format fosters a sense of belonging and shared identity. The intervention is expected to promote emotional regulation through sustained engagement with emotion-focused creative tasks, self-concept through the experience of competence and the valorization of each child’s artistic production, relational security through the consistency of the same facilitator throughout the project and the stable composition of preexisting peer groups, and group cohesion and agency through collaborative sharing, peer learning, and guided autonomous creative choice-making.

The program was conceived and developed by a multidisciplinary team comprising a cultural producer, a qualified art facilitator with 2 years of prior field experience working with children in the same community neighborhoods, and a psychologist.

Second, children’s final artistic products will be displayed in the community galleries in their neighborhood in an opening ceremony. All primary school students in Portugal follow a national curriculum that includes arts education as a mandatory subject, known as “Expressive Arts,” meaning that both the intervention and waitlist control group will have some exposure to arts activities throughout the study period. However, while the regular Expressive Arts curriculum is delivered by class teachers as part of the curriculum, our program is a structured, community-based enrichment initiative designed by a professional artist, with explicit socioemotional development goals, using materials and arts methods that differ from what is available at schools and the standard curriculum.

### Measures

The study’s design, assessment waves, variables, and measures are presented in Table 1.

**Table 1 table1:** Study design, assessments, variables, and measures.

	Baseline (T1)	Postintervention assessment (T2)
Parent or caregiver	Sociodemographic, child support services, extracurricular activities, school functioning, and parental mental and physical health historya Children’s adverse related life events exposure (PEARLSb) Resource use (RUQc)	Sociodemographic, child support services, extracurricular activities, school functioning, and parental mental and physical health history a Children’s adverse related life events exposure (PEARLSb) Resource use (RUQc)
Teacher or technician	Children’s psychosocial adjustment (SDQd)	Children’s psychosocial adjustment (SDQd)
Child	Self-concept (PSPCSA-YCe and SPPCf) Health-related quality of life (CHU-9Dg)	Self-concept (PSPCSA-YCe and SPPCf) Health-related quality of life (CHU-9Dg)

^a^Questionnaire on sociodemographic characteristics, child support services, extracurricular activities, school functioning, and parental mental and physical health history.

^b^PEARLS: Pediatric Adverse Childhood Experiences and Related Life Events Screener.

^c^RUQ: resource use questionnaire.

^d^SDQ: Strengths and Difficulties Questionnaire.

^e^PSPCSA-YC: Pictorial Scale of Perceived Competence and Social Acceptance for Young Children.

^f^SPPC: Self-Perception Profile for Children.

^g^CHU-9D: Children’s Health Utility-9D.

#### Sociodemographic Data

The caregiver will report on themselves and on the child’s age and gender, as well as their own education, marital status, employment status, perceived relative income, housing status, nativity or residence, and number of biological and nonbiological children.

#### Self-Reported Mental Health History

Caregiver’s mental health will be assessed through self-report items on the history of mental health diagnosis, current mental health problems, and receipt of treatment. Response options will include self, other parent or caregiver, both, no, do not know, and prefer not to answer. For those receiving treatment, the type of treatment was recorded (medication, professional support or psychotherapy, both, or other).

#### Child Support Services, Extracurricular Activities, and School Functioning

The caregiver will report on the child’s receipt of support services (current or past), specifying the types of support received. Additionally, caregivers indicate the child’s current participation in extracurricular activities, including the frequency per week. School-related information will also be collected, encompassing grade repetition, school attendance (including the number of unexcused absences), and parent-rated assessments of the child’s behavior and academic performance.

#### Adverse Related Life Events

Parents will report on their children’s RLE, which will be assessed using part 2 of the Pediatric Adverse Childhood Experiences and Related Life Events Screener (PEARLS) [34]. The 7 questions include physical illness or disability of a caregiver, death of a caregiver, housing instability, forced separation from caregiver, exposure to discrimination, food insecurity, and community violence. We will categorize the 7 RLE responses as “no RLEs,” “1-3 RLEs,” and “≥4 RLEs.”

### Primary Outcome

The Strengths and Difficulties Questionnaire (SDQ [35,36]; Portuguese version [37]) is a behavioral screening tool comprising 25 items and an impact supplement. Intended for educators and teachers, it is applicable to children, with a specific version available for school-age children (aged 4 to 17 years) [36]. On the basis of the child’s behavior in the last 6 months, respondents are required to mark 1 of 3 responses: “not true,” “somewhat true,” and “certainly true.” The 25 items are distributed across 5 scales, with 4 representing problematic behaviors (emotional symptoms, conduct problems, hyperactivity, and problems with peer relationships), and one scale assessing prosocial behavior. Results are obtained by summing the values of the items in each scale and are interpreted as normal, borderline, or abnormal based on standardized values (minimum 0 and maximum 10 for each scale). The impact supplement, intended for educators and teachers, addresses the chronicity of the problem, level of stress, social adjustment of the child, and burden associated with the problem for others. This questionnaire has been widely used in research on externalizing behavior problems. Studies indicate internal consistency ranging between 0.65 and 0.85 for the teachers’ version [38].

